**Treatment services and adverse events**				
Program and client costs (PACC-SAT) [126–128]	Treatment utilization and cost, mediator	X	X	
Adverse events (SAFTEE) [129]	Safety outcome		X	X
**Process measures**				
Project EHNANCE session completion, duration	Process	BNI and telephone booster		
Yale adherence and competence rating scale, adapted [130]	Intervention fidelity	BNI sessions only		
**Implementation-related measures**				
Cost-related data	Cost effectiveness	X	X	X
Participant satisfaction	Evaluation		X^a^	X^a,c^

^a^Indicates participant self-administered via survey

^b^Verified with objective measures at follow-up for outcome ascertainment [55, 131]

^c^Completed at 90 day assessment only if not completed at 34 day assessment

A secondary outcome of AUD treatment engagement is potential change in use and cost of health services from before the index hospitalization to a comparable period following hospital discharge. Reduction in health service use and costs would be a cost-savings outcome (i.e., benefit of the intervention) [58]. Even if these health service use and cost savings do not completely compensate for intervention costs, they could at least reduce net intervention cost. Emergency department, outpatient, and inpatient visits as well as medication before and after hospitalization will be extracted from the electronic health record for the 12 months before and following hospitalization. Intervention costs themselves will be assessed by multiplying provider and patient time spent for each patient in each intervention condition by provider and patient self-reported wage rates including employment perquisites, plus any materials, medication, and other resources used in interventions. These costs, and costs of computers and software used in CBT4CBT conditions will be assessed using methods developed in previous research published by several of the current authors [58].

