
### Study aims and hypotheses

Among 450 hospitalized individuals with untreated moderate to severe AUD (by Diagnostic and Statistical Manual-5 [DSM-5] criteria), our aims are to evaluate the effectiveness of hospital-initiated BNI vs. BNI + MAUD vs. BNI + MAUD + CBT4CBT on AUD treatment engagement at 34 days (primary outcome) and 90 days post-discharge; changes in alcohol use by self-report and biomarker over the 90 day period; and (exploratory) health care utilization, including Emergency Department visits and hospital readmission (Aim 1). We hypothesize that BNI + MAUD + CBT4CBT will be more effective than BNI + MAUD, which will be more effective than BNI alone as evidenced by higher rates of AUD treatment engagement, and reductions in alcohol use and urgent and emergency healthcare utilization post-discharge.

We will explore whether the effectiveness of the interventions on AUD treatment engagement and alcohol use outcomes differs across and within racial and ethnic groups and by SDOH indicators that reflect sequalae of structural racism (Aim 2). We hypothesize that there will be no difference in treatment effectiveness by race or ethnicity after adjustment of confounders but there will be differences based on SDOH.

Consistent with our prior experiences [40], we will additionally conduct an implementation-focused process evaluation [21], involving process measures, a clinician and staff survey, in addition to obtaining measures of the amounts and unit costs of resources used to implement each intervention to patients as well as health care staff. Analyses of cost, cost effectiveness, possible cost-savings benefits from reduced use of health care following the intervention, and cost–benefit for each intervention will compare individual-level provider and patient costs, indices of cost-effectiveness, and indices of cost–benefit for the three intervention combinations, as well as intervention-level indices of incremental cost-effectiveness ratios (ICERs) [41, 42] (Aim 3).

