#### Statistical analyses

##### Primary and secondary outcomes

The primary objective of this analysis will be to determine if the proportion of participants with formal AUD treatment engagement (yes/no) at 34 days post-discharge differs among those randomized to BNI alone, BNI + MAUD, and BNI + MAUD + CBT4CBT in this diverse sample. The primary outcome (1a) of AUD treatment engagement is binary and we will use logistic regression with two planned contrasts to evaluate statistical significance of the differences in proportion of formal AUD treatment engagement (as verified through electronic medical record and/or contact with treatment facility). This statistical model will also be used to assess efficacy of study interventions on AUD treatment engagement at 90-days following randomization (1a). Secondary outcomes (1b) will include change in the self-reported percentage of heavy drinking days (PHDD) by month from the 30-day period prior to hospitalization (baseline) to the 34- and 90-day post-discharge timepoint, which will be evaluated with random effects regression statistical models. These models have several advantages in follow-up data from clinical trials of individuals who use substances, as they are less vulnerable than traditional MANOVA approaches to missing data [85, 86]. An additional secondary outcome will include change in biomarker PEth, which as a continuous outcome will be evaluated with a similar statistical approach. Given limited data on factors impacting PEth levels among hospitalized patients [87] and building from our own experiences [88], we will also evaluate the correlation between baseline self-reported alcohol use (in the 30-day period prior to hospitalization) and PEth levels (e.g., liver disease, hemoglobin [38]), factors associated with PEth levels adjusting for baseline self-reported alcohol use, and factors impacting change in PEth from baseline to follow-up. Exploratory outcomes of healthcare utilization, including rates and costs of emergency department visits and hospital readmissions during the 34- and 90-day post-discharge period will be evaluated with mixed model ANOVAs. Analysis of treatment effects on primary, secondary, and exploratory outcomes will include the following contrasts: *H1:* BNI + MAUD > BNI; BNI + MAUD + CBT4CBT > BNI + MAUD or BNI.

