Intervention-level cost per engaged patient will be calculated, along with increments in this cost as successive interventions are added. We will conduct analyses to determine the type, amount, and monetary values (i.e., costs) of the major resources used to implement each intervention for each patient, including time of professionals and patients, medication, and other intervention materials and resources. Combining cost with effectiveness data for individual patients will make possible descriptive scattergrams and group-level graphs of effectiveness = *f* [costs] and benefits = *f*[costs] as well as statistical analyses comparing effectiveness/cost ratios (e.g., change in PHDD per $100 of resources consumed by intervention) and other indices of relationships between costs and effectiveness for patients in each intervention condition. Average and median effectiveness/cost will be compared statistically for each condition with individual-level effectiveness and costs [58]. Cost per effectively treated patient also will be calculated at the group level, defining effective treatment according to quantitative definitions of clinically meaningful change in alcohol use. Similar analyses will examine graphically and statistically cost–benefit relationships as expressed by individual-level net benefit (i.e., reduction following intervention in costs of ED and readmission minus costs of intervention) [58]. Further, building on a mixed-methods evaluation that informed the study protocol [44], we will conduct a survey of hospital-based clinicians and staff upon conclusion of the clinical trial regarding their perspectives on the alcohol treatment interventions and necessary supports to sustain delivery of these interventions outside of the research infrastructure. We will also capture factors that may contribute to inequitable care among historically minoritized racial and ethnic groups.

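### Net benefit is a plain pre-to-post fall in cost with no rule for deaths, so cost-free time after death can be scored as a saving

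*Protocol article*

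**What the plan says.** The text after Table 2 in the protocol article's Data collection protocol section describes a change in use and cost of health services "from before the index hospitalization to a comparable period following hospital discharge". It treats a fall as the economic benefit: "Reduction in health service use and costs would be a cost-savings outcome (i.e., benefit of the intervention"). ED, outpatient and inpatient visits and medication "will be extracted from the electronic health record for the 12 months before and following hospitalization".

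The section Implementation-focused process evaluation turns this into an individual index, net benefit, given as "reduction following intervention in costs of ED and readmission minus costs of intervention". That definition covers ED and readmission cost only and names no time window. The section Primary and secondary outcomes uses other windows for the same kind of cost: "rates and costs of emergency department visits and hospital readmissions during the 34- and 90-day post-discharge period".

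Under Study aims and hypotheses, Aim 3 compares "indices of cost–benefit for the three intervention combinations" at the individual level. The Abstract adds benefit/cost ratios and individual-level graphs of benefits against costs.

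The article does not say how a participant who dies after discharge enters these indices. Mortality is mentioned as background and as something the research hopes to reduce, but it is not named as an outcome. Adverse events are collected at 34 and 90 days.

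**The concern.** A simple difference, cost before minus cost after, treats every month without cost as a good month. That is reasonable for a survivor who no longer needs the ED. It is not reasonable for someone who has died: the record shows no cost, and the formula reads the absence as benefit of the intervention.

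Deaths are foreseeable here. Participants are medical inpatients with moderate to severe alcohol use disorder, which the Introduction calls a major cause of mortality. The exclusion for life-threatening or unstable conditions applies only where the condition prevents participation.

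What is at stake is the Aim 3 cost-benefit comparison. If one strategy prevents deaths, its survivors go on generating cost while decedents in the other arms do not, and the index can penalise the better arm. The individual-level graphs, which the Abstract intends to be usable by community representatives, could also plot a decedent among the favourable results.

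**Working it through.** The article states no figure that can be reproduced: it gives no death rate, no prior-year cost and no cost of end-of-life care. The check applies the article's own definition to assumed values.

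**Inputs**
- From the article: benefit = cost before minus cost after; 12-month extraction on each side; 150 participants per arm.
- Assumed: prior-year cost C; death at month m after discharge; end-of-life cost T as a share of C; a cost rate that does not otherwise change, so that the true benefit is zero.

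**Step 1. One decedent, 12-month window.** Post-discharge cost is C × m/12 + T × C, so

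apparent benefit = C × (1 − m/12 − T).

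| Death at | T = 0 | T = 0.5 | T = 1 |
|---|---|---|---|
| month 1 | 92% of C | 42% | −8% |
| month 3 | 75% | 25% | −25% |
| month 6 | 50% | 0% | −50% |

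The apparent saving vanishes at T = 1 − m/12 and becomes a loss above that. If C is near zero, so is the saving.

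**Step 2. Difference between two arms.** Spurious difference per participant = (difference in death rates) × C × (1 − m/12 − T). With assumed deaths of 10% against 5% and C = $20,000, 0.05 × 20,000 = $1,000, and the advantage to the arm with more deaths is:

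| Death at | T = 0 | T = 0.5 | T = 1 |
|---|---|---|---|
| month 1 | $917 | $417 | −$83 |
| month 3 | $750 | $250 | −$250 |
| month 6 | $500 | $0 | −$500 |

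With 6% against 3% and T = 0, the figures are $550, $450 and $300. C = $10,000 halves all amounts and C = $40,000 doubles them.

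**Step 3. Effect of the window.** Take death on day 20, T = 0, C = $20,000 spread evenly over the year, and a pre-period of the same length W as the post-period. The apparent saving is 20,000 × (W − 20)/365:
- W = 365 days: 20,000 × 345/365 = $18,904
- W = 90 days: 20,000 × 70/365 = $3,836
- W = 34 days: 20,000 × 14/365 = $767

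The unnamed window therefore matters a great deal. A shorter window would also contain fewer deaths.

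**Step 4. Matching on days alive.** Compare the post-discharge cost, C × m/12 + T × C, with a pre-period of m months, C × m/12. Apparent benefit becomes −T × C. For death at month 3 with C = $20,000:
- T = 0: the rule as written gives 20,000 × 0.75 = +$15,000; matched, $0.
- T = 0.5: the rule as written gives 20,000 × 0.25 = +$5,000; matched, −$10,000.

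Time after death no longer earns a saving, and actual end-of-life cost still counts.

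**Step 5. Which indices are exposed.** Net benefit and the benefit/cost ratios use the cost fall. Cost per engaged patient and "change in PHDD per $100 of resources consumed by intervention" do not, so this mechanism does not reach them.

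**The case against.** The strongest reply is that this is detail a condensed article leaves to a fuller plan. The post-discharge period is called comparable without definition, which could allow matching on time at risk, and the article cites earlier work for its costing methods. A rule for deaths may exist there. This stands as a caution. However, the article itself states the benefit definition and the net-benefit formula, and both give a perverse result for a foreseeable group if followed as written.

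Several stronger readings are tempting, and the documents do not support them:
- **Every early death is a large saving.** Deaths often follow an ED visit or readmission, which are the costs that net benefit counts. Step 1 shows the sign can reverse.
- **The rule is a 12-month fall in total cost.** Twelve months is the extraction window. The net-benefit definition names no window and covers ED and readmission cost only.
- **The arm with more deaths looks better value throughout.** Two of the planned indices do not use savings at all.
- **One or two chance deaths would reorder the arms.** At most, one extra death with C = $20,000 adds 20,000/150 = $133 per participant. If individual cost change has an SD of $20,000 (assumption), the standard error of an arm difference is 20,000 × √(2/150) = $2,309, so $133 is about 6% of it; three deaths ($400) are about 17%. With an SD of $10,000 the shares are about 12% and 35%. A chance imbalance in a randomized comparison is noise; the systematic distortion arises if the interventions truly affect survival.
- **The artefact rivals the arms' difference in intervention cost.** Intervention cost includes medication, and no figure for it is given.

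**Conclusion.** The point holds in limited form. As defined, benefit and individual net benefit can score a death in the post-discharge window as a cost saving, and an arm that keeps more patients alive can look worse on the cost-benefit and net-benefit indices. Nothing in the article corrects this.

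The size and sign cannot be fixed from the documents. They depend on prior-year cost, end-of-life cost, time of death and the window. Under the assumptions shown, a decedent with no true change in cost rate scores between +92% and −50% of prior-year cost. A difference of five percentage points in deaths shifts mean net benefit by between +$917 and −$500 per participant at $20,000 of prior-year cost. Either sign reflects the definition and not any effect on care needs among the living, apart from the end-of-life cost itself.

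The effect is confined to part of Aim 3. The primary outcome, the alcohol outcomes and the engagement-based cost indices are untouched.

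**What to change.** In the Data collection protocol and Implementation-focused process evaluation sections:

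1. State that time after death does not count as a saving. For a participant who dies, compare post-discharge cost over days alive with a pre-admission period of equal length, and say how that period is chosen.
2. Name one window for net benefit and reconcile it with the 12-month extraction and the 34- and 90-day cost analyses.
3. Report deaths by arm beside net benefit.
4. Show the unadjusted pre-post version as a sensitivity analysis.

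This needs analysis wording and dates of death, with no extra visits. The costing becomes slightly more complex, and a short matched period gives a noisier estimate for early deaths. Deaths outside the health system may be missed in the electronic record, so the source of dates of death should be stated.

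A utility-weighted net benefit is not proposed: the PROPr utility measure stops at day 90, and the article gives no monetary value per unit of utility.

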### Intervention components overview

#### Brief negotiation interview with telephone booster (BNI)

All participants receive the BNI with referral to aftercare AUD treatment and opportunity for a 2-week telephone booster delivered by a dedicated trained Health Promotion Advocate (HPA). The BNI contains the essential components of effective brief interventions [59–64] and includes training materials that have been used to train non-specialists in various clinical settings. First developed and evaluated in the YNHH Emergency Department (ED) [63–65], the purpose of the BNI is to assist patients in recognizing and changing levels of alcohol consumption that pose health risks. It relies on strategies from motivational interviewing (MI) and the stages of change model [66]. The main goals are to: (1) decrease ambivalence about reducing alcohol use; and (2) negotiate strategies for change. During the 15–20 min BNI, the HPA will: (1) *Raise the subject* of alcohol use; (2) *Provide feedback*: review the patient’s alcohol consumption, make a connection to the patient’s medical condition and reason for hospitalization; review guidelines for lower risk alcohol use; (3) *Enhance motivation*: via a readiness change ruler, which can assist in developing discrepancy; and (4) *Negotiate and Advise*: negotiate goal, provide feedback, ask patient to complete drinking agreement; summarize and arrange follow-up. Participants are provided a pamphlet regarding the impact of AUD on health and potential treatment resources (Additional files: 1, 2). The BNI session follows a structured encounter form and is digitally recorded for fidelity monitoring purposes. Consistent with our prior approaches [67, 68], the ED-based BNI manual was adapted by our team for relevance to racially and ethnically diverse hospitalized patients with AUD. All participants will be referred for formal AUD treatment per American Society of Addiction Medicine (ASAM) criteria [57] prior to discharge for ongoing AUD treatment. For this trial, we considered this the “control” condition given that this is consistent with standard of care [69] and we anticipate our approach guided by an interdisciplinary team with diverse perspectives and expertise will bolster this standard.

#### Facilitated provision of MAUD

For participants randomized to either BNI + MAUD or BNI + MAUD + CBT4CBT, the HPA provides education and counseling regarding MAUD as part of the BNI to the participant and communicates to the primary medical team that MAUD should be considered. Informed by existing resources and guidelines [70, 71], participants receive a pamphlet regarding MAUD (Additional files 1) and, via a note in the EMR, clinicians and staff are provided information regarding MAUD, including how to access the AUD treatment care signature pathway, with documentation of any stated preferences of the participant regarding a particular form of MAUD. Consistent with an effectiveness study, ultimate prescribing of any medication and the choice of medication is at the discretion of the primary medical team with the participant, and medications are provided via usual means.

#### CBT4CBT

For participants randomized to BNI + MAUD + CBT4CBT, the HPA gives the participant a username and password to access the web-based program on a provided tablet or their own device and encourages the participant to begin accessing the modules during their hospitalization (Additional files: 1, 2). Participants may continue accessing the program after discharge from the hospital. Available in English and in a culturally-adapted, Spanish version [35], this highly secure seven module program is modeled closely after the evidence-based NIAAA CBT treatment manuals [72]. Eight independent randomized trials have demonstrated the efficacy of CBT4CBT at improving substance use outcomes across diverse settings and populations [34, 35, 73–78].

#### Intervention training and monitoring

Training of HPAs includes didactics and practice exercises in both: 1) MI and 2) the BNI and its components. The MI portion of the curriculum includes 2 half-day training sessions: 3 h of instruction, beginning with an introduction to the fundamentals of MI (i.e., MI spirit and technical skills) and evidence of its effectiveness on reduction of alcohol use [79–82]; and 3 h of skills-based practice exercises using medical setting patient-specific cases. Similarly, the BNI section of the curriculum includes 2 half-day training sessions: 3 h of instruction, beginning with guidance on the steps of the BNI and support of its use among patients presenting in medical settings [64, 83, 84]; and 3 h of skills-based practice exercises. The following sections describe the critical components and training processes of MI and the BNI implemented in preparing the HPAs.

Prior to beginning study activities, HPAs were individually trained over 4 half-day workshops by a licensed psychologist with extensive experience in MI (Table 3). After this, the HPA demonstrated their acquired BNI skill with a final patient case. The patient case portion of the curriculum took 30 min. The case was specific to the study patient population and setting. The trainer was the patient actor and directly observed the implementation of the BNI. Feedback was provided at the time of the encounter. As indicated, to gain comfort and skills with working in the hospital setting and the outpatient AUD treatment referral network, the HPA additionally spent 2 days shadowing existing hospital-based HPAs who work in conjunction with YAMCS.

**Table 3 Tab3:** Health promotion advocate motivational interviewing and brief negotiation interview training plan

Training agenda	Description of training
Motivational interviewing	
Half day 1	Introduction to the fundamentals of motivational interviewing: • Prochaska and DiClemente’s Transtheoretical Model^66^ • MI spirit (i.e., partnership, acceptance, compassion, evocation) • MI technical skills (i.e., open questions, affirmations, reflective listening, summaries [OARS] [132]) • Strengthening of change talk (i.e., self-statements that support change) and skillful handling and reduction of sustain talk (i.e., self-statements that support the status quo)^90^
Half day 2	OARS skills building using various practice exercises: • Development of open questions that pull for change talk, construction of reflective statements, and identification of strengths in patient statements Practice implementation: • Role-play demonstrations and simulated patient practice exercises with performance-based feedback
Brief negotiation interview	
Half day 3	Introduction of the BNI 4-step interviewing technique: • Didactic portion included instruction on (1) how to raise the subject of alcohol, (2) provide feedback on the patient’s drinking levels, (3) enhance motivation to reduce or stop drinking, and (4) negotiate and advise a plan of action [133] • Instruction of the implementation of the BNI from a SDOH lens and structural racism context • Watch video clips on the implementation of the BNI with patients in the emergency department to learn each step [134] • Watch recordings of the *Project ENHANCE* conference lecture series
Half day 4	Practice the BNI steps with the trainer: • Role-play demonstrations with patient facing pamphlets and documentation of patient treatment agreement • Live performance-based feedback was provided by the trainer

Adapted from the ED-based BNI manual [53, 65], the HPAs are provided with the *Project ENHANCE* intervention manual, structured encounter forms, and patient-facing pamphlets. The BNI session is audio recorded and reviewed periodically by a clinical psychologist to ensure fidelity to the intervention using a checklist (Additional file: 2) and feedback is provided at least weekly. Further, the HPAs are provided the opportunity to participate in a monthly teleconference with study investigators to reflect on experiences with delivering the intervention and intervention fidelity, with particular attention to considerations on how best to address SDOH and structural racism in the context of the BNI.

Costs of training and subsequent validation via demonstration included trainer and HPA time and materials. These costs were divided among the number of participants receiving interventions, plus the additional number of participants who could have received interventions from trainees over the subsequent year(s).

